**Table 3. Examples of published estimates of cost-effectiveness and facility performance**

| **Treatments** | **Published estimates of cost-effectiveness** | **Number of patients treated** |
| --- | --- | --- |
| Preventing Maternal to Child Transmission | Sweat (2004),[[22]](#endnote-23) | Number of pregnant women with HIV who are referred to PMTCT |
| Cotrimoxazole prophalaxis | Pitter (2007), Error: Reference source not found Yazdanpanah (2005)Error: Reference source not found | Number of HIV+ patients in general care who are prescribed daily Cotrimoxazole therapy |
| Anti-retroviral Therapy | Goldie (2006),[[23]](#endnote-24) Badri (2006)[[24]](#endnote-25) | Number of ART naïve HIV+ patients who are eligible for ART who are started on 1st line ART therapy |
| DOTS for Tuberculosis | Baltussen[[25]](#endnote-26) | Number of TB patients detected and cured under directly observed treatment short course (DOTS) |
| Malaria treatment with artemisinin-based combination therapy (ACT) | Morel (2005)[[26]](#endnote-27) | Number of patients with a positive laboratory test for malaria (blood smear) who are treated with ACT |

The original data will be combined with published estimates on the effectiveness of treatments. In Table 3, columns 1 and 2 present examples of treatments that will be featured in the OSS and published estimates of their cost and effectiveness. Column 3 presents data on the number of patients treated that will be collected as indicators of the effectiveness of OSS (i.e. B3 in Table 2).

The cost-effectiveness analysis will be based on WHO’s Choosing Interventions that are Cost-Effective (CHOICE)[[27]](#endnote-28) from a health sector budget perspective.[[28]](#endnote-29) Although the United States Panel on Cost-Effectiveness in Health and Medicine recommended that all cost-effectiveness analyses include a reference case from the social perspective,[[29]](#endnote-30) the most important difference between the health sector budget and social perspectives is the omission of patient and family costs, such as informal home care, patient time when using health services, and transportation costs. Data will not be collected on patient time and transportation costs. Some experts have advised that including informal home care and patient time in cost analysis adds measurement error.[[30]](#endnote-31)

The health sector perspective includes the time of health professionals. Estimates of the cost of the capacity-building intervention will include the opportunity cost of time when health professionals are away from the site at IDI and on-site participating in OSS. District and facility personnel records will be used to identify the profession of participants and the average salary for that profession will be used in the cost estimates.

Original data on the costs of treatments will also be collected, including staff, drugs and laboratory tests. The cost of staff time will be calculated as the opportunity cost of time as described above. The cost of drugs and laboratory tests will include: HIV test kits, cotrimoxazole, first line ART, TB drugs, coartem, reagents for laboratory tests. Data on the quantities of the drugs and reagents reported on stock cards will be multiplied by the MOH unit price.

The published estimates of effectiveness of treatment (e.g. A3 in Table 2) will be measured in life DALYs or life years. These effectiveness measures serve as a common denominator so that costs and effects can be added across treatments. Weaver et. al. used this method to estimate the cost effectiveness of an influenza and pneumococcal vaccination program and found that a combined program was more cost-effective than a program that focused on a single vaccine.[[31]](#endnote-32)This feature is potentially the key to showing that OSS, which might appear expensive for a vertical program, would become cost-effective in the context of an integrated infectious disease capacity-building program.

A cost analysis will be conducted from the providers’ prospective, and focus on workload. Some treatments require spending more time with each patient, which may not be feasible for clinicians who see 80 or more patients per day. The treatment would be more attractive to clinicians if additional staff were trained to provide it, so that the patient load is shared among more staff. It would also be more attractive to clinicians if it reduced the number of visits per episode of illness.

Data on the allocation of time across health facility staff will be available from the revised medical form 5. For each outpatient visit, data are reported on the clinical and laboratory professional who provided care. Data are also reported on whether a patient was a “new attendance” or “re-attendance,” meaning a patient who has visited the health center more than once for the same episode of illness. These data will be used to compare the number of patients treated per clinical and laboratory professional between the intervention and control sites. The analysis will address whether or not the patient load is shared more broadly. In addition, the total number of patients treated will be compared between the intervention and control sites. The number of patients treated will distinguish between new attendance and re-attendance. As in the cost-effectiveness analysis, district and facility personnel records will be used to identify the profession of clinical and laboratory staff and the average salary for that profession will be used in the cost estimates.

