**Figure 2: Evaluation Design**

The indicators that will be collected from components 2-4 are summarized in Table 1. No indicators were collected for the Site Assessment.

|  | **Table 1 Summary of Indicators** | | | |  | | | | | |
| --- | --- | --- | --- | --- | --- | --- | --- | --- | --- | --- |
|  | | Hypothesis 1: Build clinical skills of core course trainees | | Hypotheses 2-4: Test effectiveness of on-site multidisciplinary training and continuous quality improvement | | | | | | |
|  | | Com-petency | Practice | Process indicators | | Laboratory Performance | Clinical Performance (examples) | Modeling health outcomes | | Direct measure of health outcomes or mortality |
| Effective Coverage | Cost-effective intervention (from literature) |
| HIV prevention | | Measured by case studies or case scenarios | Measured by observation of trainees at their site | 1) Staff on-site  2) Employee engagement,  3) Availability of supplies, including   - HIV test kits - cotrimoxazole - first line ART - TB drugs - coartem - reagents for laboratory tests | | HIV test  DBS | % HIV positive pregnant women with an HIV/ART card  % HIV exposed infants on CTX | Number of pregnant women with HIV who are referred to PMTCT | PMTCT | HIV exposed children who are HIV- |
| HIV care | | Blood test  Urine test  CD4 specimen | Number of HIV+ patients prescribed daily cotrimoxazole | Number of HIV+ patients on cotrimoxazole therapy | Daily Cotrimoxazole | Mortality of HIV patients |
| ART | | Number of ART naïve HIV+ patients who are eligible for ART who start 1st line ART | Number of HIV patients on ART | ART | Mortality of ART patients |
| TB/HIV | | HIV test  Sputum smear | Number of TB suspects with known HIV status  Number of TB/HIV patients started on ART within 3 months of starting TB treatment | Number of patients who are smear negative or extra-pulmonary TB detected & cured under DOTS | Full DOTS | Mortality of TB/HIV patients |
| Case mgmt of respiratory illness | | Sputum smear | Number of TB suspects sent for first AFB smear  Number of smear negative TB suspects started on empiric treatment | Number of TB patients detected and cured under DOTS  Number of children diagnosed with pneumonia | - DOTS - Case mgmt of pneumonia for children | Mortality of TB patients  and children under 5 |

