The clinical performance indicators will be based on Health Management Information System (HMIS) data or field-tested alternatives to the HMIS forms. For example, the Uganda Malaria Surveillance Program (UMSP) patient visit form will replace the medical form 5. In addition to the UMSP forms, data will be extracted from the Antenatal Care Register, Maternity Register, Post Natal Care Register, Inpatient Register, HIV/ART cards, and TB Registers, and the laboratories’ Dried Blood Spot, Polymerase Chain Reaction DBS-PCR register .

The patient visit form (or modified version of it) would be completed by the health facility staff for every patient who visits the outpatient department. The form identifies patients by their name and outpatient department number. For most records, the data base will be anonymous in the sense that the names will not be entered into the data base and the patient records will not be linked across visits. For records that involve follow-up such as a referral or initiation of TB, the data will be confidential in the sense that names will be entered in the data base so that the information can be linked to records at the referral institution or the TB registers.

For the registers and HIV/ART cards, records will be checked for accuracy and completeness and individual data will be extracted at regular intervals. The records will be confidential in the sense that identifying information will be entered in the data base so that records can be linked between registers and cards, and individuals who are lost-to-follow-up can be traced.

All of these data are routinely collected and analyzed by the UMSP at Makerere Unversity or the Ministry of Health’s Quality of Care Initiative (QCI) without undergoing human subjects/ethics review. The IDCAP evaluation is similar to other activities that seek to improve the quality of care to meet existing Ministry of Health guidelines rather than to test new procedures or medical devices.

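### The count that feeds the PMTCT part of the DALY model is women referred, not women treated; Table 1 has a parallel mismatch for childhood pneumonia

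*Protocol*

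**What the plan says.** Section 3.3.1 builds the first cost-effectiveness method by multiplying the published DALY gain of a treatment (Table 2, line A3) by the effect of the capacity-building programme (line B3). On where B3 comes from, the text after Table 3 says: "Column 3 presents data on the number of patients treated that will be collected as indicators of the effectiveness of OSS". That column is headed "Number of patients treated".

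The entries in the column are of different kinds:

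- PMTCT: "Number of pregnant women with HIV who are referred to PMTCT"
- ART: "Number of ART naïve HIV+ patients who are eligible for ART who are started on 1st line ART therapy"
- Malaria: "Number of patients with a positive laboratory test for malaria (blood smear) who are treated with ACT"
- TB: patients detected and cured under DOTS
- Cotrimoxazole: patients prescribed daily therapy

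Table 1 (section 3.0) has an Effective Coverage column within its block on modelling health outcomes. It repeats the PMTCT referral count. For childhood pneumonia it lists "Number of children diagnosed with pneumonia" and pairs this with case management of pneumonia as the cost-effective intervention. Table 3 has no pneumonia row.

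Section 3.3.1 also lists features that improve policy cost-effectiveness. One is a larger rise in the number of patients who actually use the treatment.

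**The concern.** The DALY gain multiplied by B3 is a gain from treatment. If B3 counts referrals, an effect of OSS on referral becomes averted DALYs with no evidence that prophylaxis followed. Training and quality improvement can readily change referral and recording, so the distinction matters for this intervention in particular.

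The protocol makes the distinction itself elsewhere. In Table 1, prescribing cotrimoxazole is clinical performance and being on it is effective coverage. Sending a malaria suspect for a smear is clinical performance and treating a smear-positive patient with ACT is effective coverage. PMTCT referral and pneumonia diagnosis are the two Effective Coverage entries that stop short of treatment.

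At stake is hypothesis 3, which judges the cost-effectiveness of OSS against interventions already recommended internationally. The primary comparison of performance indicators between Phase 1 and Phase 2 sites is not affected.

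**Working it through.** **Step 1: reproduce Table 2, to see how B3 enters.**

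- A3 = 0.13430 − 0.06861 = 0.06569, shown as 0.0657.
- B4 = A3 × B3. Classroom: 0.0657 × 0.05 = 0.0033. Classroom plus OSS: 0.0657 × 0.9 = 0.0591.
- B5 = 46.69 + B1 − 49.19. Classroom: 46.69 + 10 − 49.19 = $7.50. With OSS: 46.69 + 110 − 49.19 = $107.50.
- B6 = B5 / B4. Classroom: 7.50 / 0.0033 = $2273. With OSS: 107.50 / 0.0591 = $1819.

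All match the protocol. B3 enters DALYs gained linearly, so an error in the count passes through in proportion.

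**Step 2: referral in place of receipt.** Let r be the share of referred women who receive prophylaxis, equal in both phases, and let the published DALY gain be per woman treated. If OSS adds ΔN referrals, the plan credits ΔN × A3 and the benefit is r × ΔN × A3. The ratio is 1/r. An equal r in the two phases does not cancel, because it scales the difference between them.

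The protocol gives no r. Over an assumed range, using the OSS column of Table 2 only as a template with cost held at $107.50:

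| Assumed r | Overstatement 1/r | DALYs, 0.0657 × 0.9 × r | Template ICER |
|---|---|---|---|
| 0.9 | 1.11 | 0.0532 | $2020 |
| 0.8 | 1.25 | 0.0473 | $2273 |
| 0.7 | 1.43 | 0.0414 | $2597 |
| 0.5 | 2.00 | 0.0296 | $3636 |

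The last column uses hypothetical cotrimoxazole inputs. It shows direction and sensitivity and is not an estimate for PMTCT.

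**Step 3: if r differs by phase.** With referrals N1, N0 and receipt shares r1, r0, the true gain in women treated is r1·N1 − r0·N0 = r1·(N1 − N0) + (r1 − r0)·N0. If OSS raises referral but not receipt, this is zero and the whole PMTCT gain is artefact. If OSS also raises the receipt share, the overstatement is smaller than 1/r1 and could reverse. The referral count cannot tell these cases apart.

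**Step 4: carry to the overall ICER.** Section 3.3.1 adds effects across treatments. If PMTCT supplies a share s of all credited DALYs and the other terms are right, the total is overstated by 1 / (1 − s(1 − r)). This runs from 1 when s = 0 to 1/r when s = 1. The protocol gives no s.

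**The case against.** **The published PMTCT figure may already allow for uptake.** If it is per woman entering a programme, multiplying by r would discount twice. By its title the cited study concerns nevirapine, not referral, but its denominator cannot be checked from the protocol. This stands as a condition on the size.

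**Follow-up of referrals is planned.** Section 3.3.1 keeps names on records that involve a referral so that they can be linked to the receiving institution. The Data Storage part of section 3.3.5 describes checking registers and HIV/ART cards for whether the follow-up took place. This stands, and it makes the repair easier. Neither section says that the result enters the DALY model.

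**B3 is a measure of provider behaviour, Table 3 gives examples, and Table 1 has other HIV-prevention indicators.** Referral is indeed a provider behaviour. But the text ties B3 to a column labelled as patients treated, and the same referral count stands under Effective Coverage in Table 1, so this is more than a loose example.

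**Cotrimoxazole is open to the same criticism.** In Table 3 it is counted by prescription, a milder form of the problem. Table 1 has the stricter version, patients on therapy.

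**A reader might infer that pneumonia diagnoses are counted as patients treated in Table 3, and that better diagnosis would register as lost DALYs.** The documents do not support that. Pneumonia is absent from Table 3, and no published pneumonia DALY estimate is named. A wrong sign would arise only if the Table 1 count were multiplied by such an estimate and OSS reduced over-diagnosis.

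**Conclusion.** The point holds for PMTCT. In both tables the quantity that feeds the model is referral, under a heading and in a column that otherwise mean treatment. Under the stated assumptions (published estimate per woman treated, same r in both phases) the PMTCT component of benefit is overstated by 1/r, which is 1.1 to 2.0 for assumed r from 0.9 down to 0.5.

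A reader might go further and conclude that the ICER for hypothesis 3 is shown to be biased by that factor. It is not: r, the PMTCT share of DALYs and the denominator of the published estimate are all missing from the protocol, so the effect on the combined ratio is unknown.

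For childhood pneumonia the inconsistency is real but confined to Table 1, and its effect on the model is conditional. The definitions should be corrected before the cost-effectiveness analysis.

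**What to change.** 1. In Tables 1 and 3, define PMTCT effective coverage as the number of HIV-positive women (or mother-infant pairs) recorded as having received prophylaxis. Section 3.3.1 already says "data will be extracted from the Antenatal Care Register, Maternity Register, Post Natal Care Register", along with HIV/ART cards, and the referral linkage is planned.
2. In Table 1, define the pneumonia count as children diagnosed with pneumonia and recorded as treated for it.
3. Keep referral and diagnosis as clinical performance indicators.
4. Where receipt is not recorded, multiply the count by a completion share and vary that share in the one-way sensitivity analysis of section 3.3.2. First confirm whether the published PMTCT estimate already includes uptake, so that it is not discounted twice.

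The cost is a change of two definitions, with no new sample or design. The protocol lists the registers and forms but not their fields, so some receipt entries may be missing and the completion share may be needed more often than hoped. The credited benefit will probably be smaller.

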For specific objective 4, cost-effectiveness will be estimated with two methods. The first method is a model that combines original data on the performance indicators described in Table 1 at 36 sites and the cost of the capacity-building programs with published estimates of the cost of treatment and DALYs saved. The second method is based on original data on mortality of children under five years as described in Section 3.4 below, instead of performance indicators and DALYs. In other words, the denominator of the incremental cost effectiveness ratio will be measured two ways: economic modeling in which effectiveness is measured by original data on performance indicators and published estimates of the effect of the performance indicators on DALYS, and b) estimates in which effectiveness is measured with original verbal autopsy data on mortality.

The first method was proposed by Mason et. al. to estimate “policy-cost-effectiveness.”[[19]](#endnote-20) Their method grew out of observation that many cost-effective treatments were not adopted by providers. For example, the cost-effectiveness of co-trimoxazole prophalaxis is well established. Pitter et. al estimated that providing it to all HIV-infected people is cost-saving ($2.5 per person year) and providing it only to people in WHO clinical stages 2, 3, and 4 cost $22.23 per DALY gained relative to no prophalaxis.[[20]](#endnote-21) Yazdanpanah et.al. estimated that providing it to people in WHO clinical stages 2, 3, and 4 cost $150 per life year saved relative to no prophalaxis.[[21]](#endnote-22) This evaluation does not seek to replicate the cost-effectiveness analysis of this treatment. It evaluates the cost-effectiveness of a capacity-building intervention that promotes the adoption of the treatment at health facilities.

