| **A. Pitter et.al. estimates** |  |  | |
| A1. Net treatment cost | $49.19 | $46.69 | |
| A2. Number of DALYS lost | 0.13430 | 0.06861 | |
| A3. Incremental benefit, i.e.DALYS gained |  | 0.0657 = 0.13430 - 0.06861 | |
| A4. Incremental cost |  | -$2.5 = $46.69 - $49.19 | |
| A5. Incremental cost-effectiveness ratio |  | Cost saving | |
| **B. Estimates with capacity-building** |  | **Classroom training** | **Classroom training plus OSS** |
| B1. Training cost |  | $10 | $110 |
| B2. Net program cost with training |  | $56.69  = $46.69 + 10 | $156.69  = $46.69 + $110 |
| B3. Effectiveness of training program at changing provider behavior |  | 5% | 90% |
| B4. Incremental benefit, i.e. DALYS gained |  | 0.0033  = 0.0657 * 0.05 | 0.0591  = 0.0657 * 0.9 |
| B5. Incremental cost |  | $7.50 | $107.50 |
| B6. Incremental cost-effectiveness ratio |  | $2273  = $7.50 / 0.0033 | $1819  = $107.5 / 0.0591 |

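### The cost-effectiveness template uses B3 as a proportion against per-person costs, but the protocol fills B3 with patient counts and leaves treated time unmatched

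*Protocol*

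**What the plan says.** Section 3.3.2 (Design) states that the cost-effectiveness analysis will follow the calculation shown in Table 2. In that table (Section 3.3.1) the row "B3. Effectiveness of training program at changing provider behavior" holds 5% for classroom training and 90% for classroom training plus OSS. The row multiplies the DALY gain, which is derived as "0.0657 = 0.13430 - 0.06861". The cost rows are amounts for one person.

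The paragraph after Table 3 says: "Column 3 presents data on the number of patients treated that will be collected as indicators of the effectiveness of OSS", and it identifies these data with row B3 ("collected as indicators of the effectiveness of OSS (i.e. B3 in Table 2"). The cotrimoxazole entry, for example, is "Number of HIV+ patients in general care who are prescribed daily Cotrimoxazole therapy". The other four entries are counts too. In Table 1, the effective-coverage column under the modelling of health outcomes also lists numbers of patients.

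On time, Section 3.3.1 reports from the published cotrimoxazole study that "providing it to all HIV-infected people is cost-saving ($2.5 per person year", closing the bracket there. The DALY rows of Table 2 carry no time unit. The Phase 1 versus Phase 2 comparison is made at month nine.

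Section 3.4.1 refers to B3 as the incremental benefit and to B4 as the incremental cost. In Table 2 the incremental benefit is B4 and the incremental cost is B5.

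**The concern.** Row B3 is given three meanings: a proportion in Table 2, a count under Table 3, and a DALY benefit in Section 3.4.1. The template accepts only the first. It holds cost at the level of one person, so a count entered in B3 multiplies the DALYs by the number of patients and leaves the cost unchanged.

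Table 2 is the only arithmetic the protocol gives for specific objective 3 and hypothesis 3, and it supplies the first of the two methods compared under objective 4. Section 3.3.1 also plans to add costs and effects across treatments, which requires a common unit. An analyst following the text cannot tell what to enter, and two analysts could report ratios that differ by a large factor from the same data.

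**Working it through.** **Inputs, all from Table 2.** Net treatment cost $49.19 without and $46.69 with prophylaxis; DALYs lost 0.13430 and 0.06861; training cost (B1) $10 for classroom and $110 with OSS; B3 of 5% and 90%.

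**1. Reproduce the stated ratios.**
- A3 = 0.13430 − 0.06861 = 0.06569, shown as 0.0657. A4 = 46.69 − 49.19 = −$2.50.
- Classroom: B5 = 56.69 − 49.19 = $7.50. B4 = 0.0657 × 0.05 = 0.0033. B6 = 7.50 / 0.0033 = $2,273 ($2,283 unrounded).
- With OSS: B5 = 156.69 − 49.19 = $107.50. B4 = 0.0657 × 0.9 = 0.0591. B6 = 107.50 / 0.0591 = $1,819 ($1,818 unrounded).

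Both stated figures are recovered, and only with B3 as a proportion.

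**2. See what B3 acts on.** B5 equals B1 − 2.50 in both columns, so the full treatment saving is taken whether 5% or 90% are treated. B3 enters the denominator only. If the saving were scaled by B3:
- Classroom: (10 − 0.05 × 2.50) / 0.0032845 = 9.875 / 0.0032845 = $3,007.
- With OSS: (110 − 0.9 × 2.50) / 0.059121 = 107.75 / 0.059121 = $1,823.

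**3. Enter a count as the text under Table 3 directs.** With n patients in B3 and the per-person cost kept, the ratio is 107.50 / (0.06569 × n). The values of n are assumed, because the protocol gives none.

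| n (assumed) | Denominator | Result |
| --- | --- | --- |
| 50 | 3.2845 | $32.73 |
| 100 | 6.569 | $16.36 |
| 500 | 32.845 | $3.27 |

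The numerator is dollars for one person and the denominator is DALYs for n people, so the result is not dollars per DALY.

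**4. Check that the mixture is the cause.** If the cost is totalled over the same n treated people, the ratio is (n × 107.50) / (n × 0.06569) = $1,636 for every n. The dependence on n in step 3 comes from pairing a total with a per-person amount.

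**5. Ask whether the regression repairs it.** Sections 3.3.2 estimates the effect as a baseline-adjusted Phase 1 versus Phase 2 coefficient and uses its confidence interval for the sensitivity analysis. For a count indicator that coefficient is in patients per site. The interval has the same unit problem.

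**6. Treated time.** Nine months is 0.75 year. If the cotrimoxazole DALY gain is per person-year, and each patient on treatment for nine months were credited with a full year, DALYs would be overstated by 1 / 0.75 = 1.33. With B3 = 0.9 and 0.75 year of treatment, the ratio is 107.50 / (0.06569 × 0.9 × 0.75) = $2,424 instead of $1,818.

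**The case against.** The best defence is that Table 2 is a hypothetical sample calculation and that the protocol leans towards totals elsewhere. Costs come from accounting and financial records and from stock-card quantities times unit prices, and effects are to be summed across treatments. A count times DALYs per patient, divided by total cost, is a valid ratio. In such a model it is right that the ratio falls when more patients are treated for a given programme cost. This stands as far as it goes: a reader might infer that the plan cannot yield a valid unit at all, and that is too strong. But the protocol never says that costs will be totalled to match the counts, and it names Table 2 as the calculation to follow.

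Table 1 does contain some percentages, and Section 3.3.1 says B3 will come from the performance indicators. Those percentages sit among the clinical performance examples. The column assigned to the model lists counts.

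Two further readings are tempting and not supported. One is that every patient is credited with a full year of benefit. No such rule is stated; the person-year unit is attached only to the cotrimoxazole cost result, and the time units of the other published estimates are not given. A larger overstatement of 2.67 (1 / 0.375) would follow if starts were spread evenly over nine months, but that pattern is an assumption, and Table 1 counts patients on cotrimoxazole rather than starts. The other is that OSS is bound to look more cost-effective than it is. Training costs are amortized over 3 to 5 years, so if the effect lasts, a one-year credit could be too short.

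A statistical analysis plan, not seen here, may hold the conversion. It would not remove the contradiction within the protocol.

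**Conclusion.** The point holds as a contradiction in the stated calculation. Table 2, made binding by Section 3.3.2, needs a proportion in B3; the text under Table 3 supplies a count; Section 3.4.1 uses the row labels in a third way. Read literally, the rule produces a figure that is not dollars per DALY.

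The size cannot be fixed from the protocol. The $33, $16 and $3 rest on assumed counts of 50, 100 and 500 and on keeping Table 2's per-person cost; they show sensitivity to the entry, not an expected error. The 1.33-fold figure is a separate matter. It applies to cotrimoxazole only, assumes that the DALY gain shares the person-year unit of the cost, and assumes a full-year credit that the protocol does not state. It should not be multiplied with the first effect. The direction of any net bias is not established.

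**What to change.** Put numerator and denominator on the same population and time base, in one of two ways.

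- **(a) Per eligible patient.** Keep the layout of Table 2. Define B3 as the baseline-adjusted Phase 1 minus Phase 2 difference in the proportion of eligible patients treated, and name the eligible denominator for each treatment. Use the amortized OSS cost per eligible patient in B1, and multiply the net treatment cost by B3.
- **(b) In totals.** Take the baseline-adjusted incremental number treated and express it in the unit of each published estimate: person-years for cotrimoxazole, and the source's own unit for the others. Incremental DALYs = incremental units × DALYs per unit. Incremental cost = total amortized OSS cost for the same period + incremental units × net treatment cost per unit.

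Both keep the 3 to 5 year amortization and the baseline adjustment already planned. Then correct the reference to B3 under Table 3, and the references to B3 and B4 in Section 3.4.1.

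The cost is a rewrite of Table 2 and a few sentences. Treated person-time should be obtainable from the HIV/ART cards, which are already to be extracted at regular intervals. Option (a) also needs counts of eligible patients. The reported ratio may change in either direction.
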